### Primary outcome

A useful way to express the primary outcome measure is the number of skin tear-free days. Each participant will enter the study with no unhealed skin tear injuries and will remain in the study (unless withdrawn prematurely) for 112 days (i.e. 16 full weeks). Therefore, each participant has the potential to experience 112 skin tear-free days. In the event of a skin tear injury, the number of days from the date of injury until the date it is healed will be subtracted from 112 to give the number of skin tear-free days. A healed injury is defined as one which has an absence of scab and full epithelial covering that does not require continuance of dressing for absorption of exudate (sometimes a dressing may be left on a healed but delicate wound for a few days after healing). The date of healing will be identified by the visiting research nurse via wound inspection during regular, approximately weekly, visits and in collaboration with care home staff as necessary. Participants who experience a skin tear injury in week 16, or who have an injury discovered at week 16, will continue to provide follow-up information beyond that date and skin tear-free days will be expressed as a proportion of the total follow-up time.

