**Figure 1 Fig1:**
[figure not shown]
Participant pathway diagram (taken from the Participant Information Sheet).

**Table 1 Tab1:** Tabulated study schedule

Study procedure	Set up (Visit 1)	Baseline/Study Day 0 (Visit 2)	Study Day 1 (the day after consent)	Upon new injury	Weekly* for 16 weeks	Study Day 112	Qualitative data collection
Identify potentially eligible participants	X						
Provide Participant Information Sheet	X						
Informed consent		X					
Collection of baseline information		X					
EQ5D-5 L questionnaire		X		X^c^		X	
ICECAP-O questionnaire		X		X^c^		X	
FES-I (short) questionnaire		X		X^c^		X	
Randomisation		X					
Provision of socks (intervention arm only)		X					
Wearing of socks (intervention arm only)			X --------------------------------- > X				
Completion of participant diary (intervention arm only)			X --------------------------------- > X				
Photograph wound				X^b^			
Measurement of wound				X^b^			
Wound scoring				X^b^			
Cardiff wound impact schedule^a^				X^c^		X^d^	
Adverse event recording			X --------------------------------- > X^e^				
Research nurse to visit care home for progress checks					X		
Patient interviews							X
Focus groups							X

^*^Regular contact (visit or telephone), approximately weekly.

^a^Completed only by participants who experienced one or more skin tear injuries during their study participation.

^b^Performed within one working day following injury.

^c^Performed seven days post-injury.

^d^Completed on Day 112 by all participants who experienced skin tear injury during the study. In addition, participants who incur an injury during week 16 (Day 106 to 112 inclusive), will also complete the questionnaire seven days post-injury.

^e^Day 112 or Day 112 + 1 to 7 days if a skin tear injury occurs during week 16.

**Table 2 Tab2:** Main eligibility criteria (inclusion and exclusion criteria)

Inclusion criteria	Exclusion criteria
Resident in a care home or living in the community and at high risk of skin tears.	Not competent to give informed consent in the opinion of the recruiting nurse.
Aged 65 years or older.	Bedbound.
Ambulatory and/or wheelchair user able to take part in daily activities within a care home or in the community.	Being treated for current lacerations or ulcers on their legs.
	Participant likely to use graduated compression stockings or similar during the intervention period.

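### Skin tear-free days: healing time is not cut at day 112, and follow-up is lengthened only for participants with a week-16 injury, so the score depends on when follow-up is extended

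*Protocol article*

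**What the plan says.** All the rules are in one paragraph of the protocol article, under Primary outcome.

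- **Measure.** "A useful way to express the primary outcome measure is the number of skin tear-free days", and "each participant has the potential to experience 112 skin tear-free days".
- **Scoring an injury.** "the number of days from the date of injury until the date it is healed will be subtracted from 112". No limit at day 112 is given.
- **Who is followed longer.** "Participants who experience a skin tear injury in week 16, or who have an injury discovered at week 16, will continue to provide follow-up information". Table 1, footnote d, fixes week 16 as days 106 to 112.
- **How those participants are scored.** They "will continue to provide follow-up information beyond that date and skin tear-free days will be expressed as a proportion of the total follow-up time".

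No extension is stated for a wound from day 105 or earlier that is already known and still open at day 112. No end point is given for the extended outcome follow-up.

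The abstract names this as the proposed primary outcome of the definitive trial. Statistical methods says the main analysis will describe it in each group. Trial objectives says that the variability of outcomes is to inform the definitive sample size.

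**The concern.** A score meant to count tear-free days in a 16-week window should depend only on what happens in those 16 weeks. Two features of the rule break this.

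1. **Outcome-dependent follow-up.** A late injury triggers the extra observation, so the added days are mainly wound days. Uninjured participants gain none. The denominator becomes a function of the outcome.
2. **Wound days outside the window.** A wound from before week 16 that is open at day 112 is scored by its full healing time. Either the healing date is not observed, because no extension covers it, or it is obtained somehow and days after day 112 are subtracted from a 112-day total.

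At stake are the mean and SD that the pilot will report for its proposed primary outcome, and a definition likely to be carried into the definitive trial.

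**Working it through.** **Inputs from the protocol.** Window 16 × 7 = 112 days, which reproduces the stated maximum. Week 16 is days 106-112.

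**Assumptions.** The protocol gives no healing times or injury rates for this setting, so ranges are used.

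**Convention.** A wound lasting h days from injury day d is open on days d to d + h − 1.

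**Step 1: individual scores.**
- Count rule as written (injury before week 16): (112 − h)/112.
- Extension rule, followed to healing past day 112 (injury in week 16): (d − 1)/(d − 1 + h).
- Fixed window: [112 − min(h, 113 − d)]/112.

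| Assumed healing | Day 105, as written | Day 106, as written | Fixed window, day 105 / 106 |
|---|---|---|---|
| 7 days | 105/112 = 93.8% | 105/112 = 93.8% | 93.8% / 93.8% |
| 21 days | 91/112 = 81.3% | 105/126 = 83.3% | 92.9% / 93.8% |
| 28 days | 84/112 = 75.0% | 105/133 = 78.9% | 92.9% / 93.8% |
| 42 days | 70/112 = 62.5% | 105/147 = 71.4% | 92.9% / 93.8% |

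If observation of the day-105 wound simply stops at day 112, it scores 104/112 = 92.9%. A 28-day wound one day later then scores 78.9%, although it leaves one more tear-free day in the window. With 7-day healing, days 105 and 106 show no discrepancy.

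**Step 2: arm means, exact.** Assume one injury per injured person, injury day uniform on 1-112, 21-day healing, and 16-week risk 40% v 20%. The mean loss per injury, in 112-day equivalents, is:
- Fixed window: (92 × 21 + 20 + 19 + … + 1)/112 = (1932 + 210)/112 = 19.125. Arm difference 0.20 × 19.125 = 3.83.
- Week 16 extended, earlier wounds cut at day 112: arm difference 4.00 (4.003/3.825 = 1.05).
- Week 16 extended, earlier wounds subtracted in full: arm difference 4.17 (4.165/3.825 = 1.09).

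For healing of 14 and 42 days the three differences are 2.638, 2.748, 2.786 and 6.863, 7.205, 8.267. Across 14-42 days the overstatement is therefore about 4-5% if earlier wounds are cut and about 6-20% if they are not.

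**Step 3: simulation with repeated injuries.** Assume 0.5 v 0.25 injury incidents per 112 days, 25% of incidents giving two tears, and lognormal healing (log-SD 0.5) with median 14, 21 or 35 days. About 7%, 10% and 17% of controls then have a tear open at day 112. About 60-80% of these were injured before week 16, outside the extension rule.

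| Scoring, against the fixed window | Difference overstated | SD overstated |
|---|---|---|
| Week 16 extended, earlier wounds cut at day 112 | about 4-5% | about 2% |
| Week 16 extended, earlier wounds subtracted in full (as written) | about 8-26% | about 7-26% |

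**Step 4: effect on sample size.** Required n is proportional to (SD/difference)².
- Same definition for both, as written: (1.07/1.08)² = 0.98 to (1.26/1.26)² = 1.00.
- Same definition for both, earlier wounds cut: (1.02/1.04)² = 0.96 to (1.02/1.05)² = 0.94.
- SD from the pilot rule but target difference set on the fixed window: 1.07² = 1.14 to 1.26² = 1.59 as written, or 1.02² = 1.04 if earlier wounds are cut.

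**The case against.** Several points on the other side have force.

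- **Little of the distortion reaches the planned sample size.** Difference and SD grow together, so the standardised difference is nearly unchanged (step 4). This stands. A reader might infer that the definitive trial will be mis-sized by the percentages in step 3. That would need the SD from one definition and the target difference from another, and nothing in the protocol proposes this.
- **Larger inflation figures.** Leaving every wound uncut, week 16 included, would overstate the difference by 11-32% and the SD by 9-30%. The protocol does not say that, because week-16 injuries are scored over a longer denominator.
- **Count against proportion.** A reader might infer that a count and a proportion are being pooled. The last clause can be read as putting everyone on the proportion scale, and days out of 112 convert by one division. The mismatch depends on the reading. The outcome-dependent follow-up and the post-window wound days remain either way.
- **Table 1, footnote e.** Its limit, "Day 112 or Day 112 + 1 to 7 days if a skin tear injury occurs during week 16", might be taken to contradict the open-ended outcome follow-up. It belongs to the adverse event recording row and does not govern how long a wound is followed for healing. There is no contradiction.
- **Full wound time is a legitimate burden measure.** This is true, and a fixed window gives a severe day-112 tear a loss of only one day. But a burden measure would follow every open wound to healing, whatever the week of injury, and would not be scored out of 112. The stated rule does neither consistently.
- **This is a descriptive pilot.** No test rests on the outcome, and working out how outcomes can be measured is part of the pilot's purpose. This stands and limits the grade.

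**Conclusion.** The concern holds as a should-fix. The stated rule lets days outside the 112-day window into the score, lengthens follow-up only for week-16 injuries, and leaves an earlier wound still open at day 112 without stated follow-up to the healing date that its score needs.

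Individual scores can be well off. With an assumed 28-day wound they are 75% and 79%, against 93-94% tear-free in the window. Arm-level effects range from small (about 4-5% on the difference, 2% on the SD) to moderate (about 8-26% and 7-26%), depending on whether earlier wounds are cut at day 112. All these sizes rest on assumed injury rates and healing times. With healing within a week the problem nearly vanishes for injuries around the day-105/106 boundary.

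The harm is to the described mean and SD. It reaches the definitive sample size materially only if that SD is paired with a target difference set on another definition. The documents do not support a claim that the definitive trial will be mis-sized or that the pilot's conclusions fail.

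**What to change.** Before analysis, define skin tear-free days for every participant as the number of days from day 1 to day 112 with no open tear. Count a tear still open at day 112 as open to day 112. If a proportion is wanted, use the same window as the denominator for all who complete it. Keep follow-up after day 112 for healing time, reported separately, and for the 7-day post-injury questionnaires. It should enter neither the numerator nor the denominator of this measure.

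**Cost.** One rewritten definition and no new data. Injury dates and healing dates up to day 112 are already to be collected, and Trial status schedules the analysis (July 2015) after data collection ends (February 2015). The definition also avoids counting overlapping tears twice. It does not settle how early withdrawals are scored, which is a separate missing-data matter.

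**Downside.** Wound time after day 112 no longer counts in this measure, so a late tear costs few days however slowly it heals. The separate report of healing time covers that.

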### Secondary outcomes

#### Skin tear assessments

There is no universally accepted classification system for the assessment of skin tears. Payne and Martin developed the first classification system in 1990, and this was updated in 1993 [1]. Problems associated with inter-rater reliability testing of the Payne and Martin classification system, and its poor utility in Australia, led to a study that resulted in the Skin Tear Audit Research (STAR) Classification System. The STAR Classification System is commonly used in Australia, with evidence of implementation reported within the UK [30].

In the main trial, skin lacerations will be measured in centimetres (length, breadth and area) and graded either according to Payne-Martin categories or the STAR Skin Tear Classification System. The photographs will inform an assessment of the reliability of the reported grading of the injury and will be performed by a tissue viability nurse specialist blinded to allocation.

Skin tear assessments will be performed upon learning of an injury, within 24 h if possible.

#### Other secondary outcome measures

Standardised measure of health status (EQ-5D-5L): collected at baseline, 16 weeks and in the event of a skin tear injury.Assessment of capability (ICECAP-O): collected at baseline, 16 weeks and in the event of a skin tear injury.Assessment of fear of falling (Short FES-I): Collected at baseline, 16 weeks and in the event of a skin tear injury.Disease-specific quality of life measured by Cardiff Wound Impact Schedule: Collected in the event of a skin tear injury and at 16 weeks (from participants who have had a skin tear).Adverse events caused by the socks.Health care resource use: collected in the event of a skin tear injury.Outcome measures for the pilot study are:Recruitment rate for homes.Proportion of participants (home residents) eligible.Recruitment rate for participants.Attrition and loss to follow up.Ascertainment of injuries.Completion and completeness of study questionnaires.Estimates of the distribution of outcome measures.Feasibility of the workload.Acceptability of the intervention to participants.Acceptability of study participation to participants.

### Withdrawal and dropout

The participants may withdraw their consent at any time. The participants will be advised that they do not have to provide a reason for withdrawing their consent but if they are willing to provide a reason when asked by the research nurse the reason will be recorded. Standard care will not be affected by a participant’s decision to withdraw from the study. Data collected prior to withdrawal will be included in the study analysis unless a participant specifically requests that their data are removed from the database. If a participant is adjudged to have lost mental capacity during the 16-week study period, that participant will be withdrawn from the study. Data already collected with consent will be retained and used in the study. No further data will be collected or any other study procedures carried out on or in relation to the participant. It is anticipated that some participants allocated to the socks group may discontinue wearing the socks but will still be happy to fill in the outcome measures at the end of 16 weeks and in the event of a skin tear.

### Adverse and serious adverse events

In the STOPCUTS study, adverse events which are not serious and not related to study participation will not be recorded or reported. Adverse events which are serious and/or related to study procedures/intervention will be recorded. Multiple symptoms should be recorded as separate events. The events will be reported to the Chief Investigator, Sponsor and the Peninsula Clinical Trials Unit on a designated report form which will capture the research nurse’s opinion on the relatedness of the event to study procedures/intervention, and also on the expectedness of the event. Adverse reactions to the socks are expected to be uncommon. The following list of potential symptoms will be used as a reference when assessing the expectedness of adverse device effects.Allergic-type skin reaction.Miliaria.Chafing.Excessive sweating under the socks.Skin tears or bruising caused by putting on or removing the socks.Pain, discomfort, numbness, swelling or any other condition caused by socks which are too tight.Falls or other accidents caused by slipping or tripping as a result of wearing the socks.

Accumulative summaries of adverse reactions will be reviewed periodically by the Trial Steering Committee.

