### Randomisation and blinding

Randomisation will be achieved by means of a Web-based system created by the Peninsula Clinical Trials Unit in conjunction with the study statistician. The participants will be allocated to the protective socks intervention or to standard care in equal proportions, using blocks of fixed size to generate the allocation sequence and achieve balance in the numbers of participants allocated to each group. Variable block sizes were considered but would provide no advantage since the number of participants recruited at each care home is likely to be small. Randomisation will be stratified by geographical area (i.e. Exeter, Exmouth/Sidmouth and Mid Devon).

The Web-based randomisation system created and maintained by the clinical trials unit will allow secure access via computers or other devices with Internet connectivity. Research nurses will be provided with log-in details and will perform randomisation from the care home by smart phone. The system ensures allocation is concealed prior to performing randomisation. Telephone randomisation will be available during working hours (09:00 to 17:00, Monday to Friday inclusive) in the unlikely event the Web-based service is unavailable.

Blinding will not be possible for participants or research nurses. Blinding is possible for the data analyst, however, by coding the group allocation in the data file.

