### Quality control

The research nurse will check completed case report forms for missing data or obvious errors before the forms are sent to the trials unit. Data will be monitored centrally for quality and completeness, and every effort will be made to recover data from incomplete forms where possible. The data manager at the trials unit will oversee data tracking and data entry and initiate processes to resolve data queries where necessary, and the trial manager will devise a monitoring plan specific to the study which will include both central monitoring strategies and study site visits if appropriate.

Participating care homes will be required to permit the trial manager or deputy or representative of the sponsor to undertake study-related monitoring to ensure compliance with the approved study protocol and applicable standard operating procedures, providing direct access to source data and documents as requested. All study procedures will be conducted in compliance with the protocol and according to the principles of the International Conference on Harmonisation Good Clinical Practice (ICH GCP). Procedures specifically conducted by the clinical trials unit (e.g. randomisation, data management, study management and study monitoring) will be conducted in compliance with the trials unit’s standard operating procedures.

A trial management team meets regularly to discuss the progress of the trial and address any issues that arise. A Trial Steering Committee, with an independent chair, independent clinician and independent statistician meets approximately every 6 months to oversee the conduct and safety of the trial.

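### The listed safety outcome and the stated committee safety summary are both defined by attribution, so as written they cannot show an excess of serious events not blamed on the socks

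*Protocol article*

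**What the plan says.** All references are to the protocol article.

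- **Recording** (Adverse and serious adverse events): "Adverse events which are serious and/or related to study procedures/intervention will be recorded". The exclusion covers the remainder: "adverse events which are not serious and not related to study participation will not be recorded or reported". A serious event is therefore recorded whether or not it is thought related. In Table 1 the rows for sock provision, sock wearing and the diary are marked as intervention arm only; the row for adverse event recording is not.
- **Routing** (same section): "The events will be reported to the Chief Investigator, Sponsor and the Peninsula Clinical Trials Unit on a designated report form". The form also captures the research nurse's "opinion on the relatedness of the event to study procedures/intervention".
- **Assessor** (Randomisation and blinding): "Blinding will not be possible for participants or research nurses". The same section says the data analyst can be blinded by coding the groups.
- **Outcome** (Other secondary outcome measures): the safety item is "Adverse events caused by the socks". Neither outcome list has another.
- **Oversight**: "Accumulative summaries of adverse reactions will be reviewed periodically by the Trial Steering Committee" (Adverse and serious adverse events). Quality control says that this committee "meets approximately every 6 months to oversee the conduct and safety of the trial".
- **Analysis** (Statistical methods): the by-group description covers skin tear-free days and the incidence and severity of lacerations. A by-arm summary of serious events is neither stated nor excluded.

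**The concern.** The trial collects what a randomised safety comparison needs, namely serious events in both arms regardless of cause. It then names an outcome and a committee summary that use only the part of those data someone has judged causal. Once an outcome is defined as caused by the socks, randomisation contributes nothing to it, because the control arm has nothing comparable to count apart from controls who buy the socks themselves.

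Falls show why this matters. The adverse events section lists falls from slipping or tripping in the socks among the possible device effects, and the Background lists falls as an ordinary cause of injury in this population. When an event is common anyway and the device could plausibly add to it, judging cause case by case is weak evidence, and comparing the arms is the natural check. A serious fall in a sock wearer that the nurse puts down to frailty would be recorded, yet would lie outside the listed outcome and, on its ordinary reading, outside the stated committee summary. Fear of falling is an outcome; falls are not.

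**Working it through.** The plan states no adverse event rate and no safety calculation, so there is no figure to reproduce. The check has a textual part and an illustration.

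**1. Which serious events reach which place, as the text is written**

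| Serious event | Recorded and sent to Chief Investigator, Sponsor, trials unit | In listed outcome | In stated committee summary |
|---|---|---|---|
| Sock arm, judged caused by socks | yes | yes | yes |
| Sock arm, judged unrelated | yes | no | no |
| Control arm, judged unrelated | yes | no | no |
| Control arm, judged related to study procedures | yes | no | possibly |

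The second and third rows are what a comparison between arms needs. Both are in the data; neither is in the outcome or the named summary.

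**2. Illustration**

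Inputs: 45 per arm (Method/design). Assumed serious event rates are 10% in controls and 20% in the sock arm. The share *q* of sock-arm serious events judged sock-related is varied over its whole range.

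Expected recorded count = n × rate:
- control: 45 × 0.10 = 4.5
- socks: 45 × 0.20 = 9

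Expected count displayed as sock-caused = 9 × *q* in the sock arm and 0 in the control arm:

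| *q* | Socks | Control |
|---|---|---|
| 0% | 0 | 0 |
| 10% | 0.9 | 0 |
| 25% | 2.25 | 0 |
| 50% | 4.5 | 0 |
| 100% | 9 | 0 |

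The true excess is 9 − 4.5 = 4.5 in every row, but the display runs from 0 to 9. Nor does the display separate an excess from none. If both arms had a 10% rate and half of the sock-arm events were attributed, it would read 4.5 × 0.50 = 2.25 against 0. That is the same as a doubled rate with a quarter attributed.

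**3. What a by-arm table could do at this size**

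Power for two proportions (two-sided 5%, normal approximation):

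Φ{[Δ − 1.96 √(2p̄(1 − p̄)/n)] / √[(p₁(1 − p₁) + p₂(1 − p₂))/n]}

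- 10% vs 20%: p̄ = 0.15; (0.10 − 1.96 × 0.0753)/0.0745 = −0.64; power about 26%.
- 10% vs 30%: p̄ = 0.20; (0.20 − 1.96 × 0.0843)/0.0816 = 0.43; power about 66%.

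The table would be descriptive. It makes the arms visible side by side but cannot rule an excess in or out.

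**The case against.** A reader might infer that the committee is shown nothing but adverse reactions, and that an unblinded opinion filters serious events before anyone can compare the arms. The text supports neither. It names one thing the committee reviews and excludes nothing. Quality control gives that committee, with its independent chair, clinician and statistician, a general safety remit under which it could ask for more. Every serious event goes to the Chief Investigator, Sponsor and trials unit whatever its relatedness. For serious events relatedness is a field on the form, not a gate, so a by-arm table remains possible at any time. For the same reason it does not follow that the pilot could not inform safety planning for the definitive trial.

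Further points on the other side:

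- **This is a condensed article.** Safety tables and committee report contents often sit in the full protocol, terms of reference or analysis plan. That disposes of any complaint about silence in Statistical methods. It does not dispose of the outcome and the committee summary, which the article does state, each with a causal restriction.
- **The terms are loose.** Adverse event, adverse reaction and adverse device effect are not defined, and relatedness also covers study procedures, which controls undergo. So the committee summary need not be empty for controls. The missing control counterpart applies firmly to the listed outcome and less firmly to the summary. Even so, the section uses adverse reactions for effects of the socks and adverse events for what is recorded, which makes the causal reading the ordinary one.
- **Risk is low and power is poor.** This is a feasibility pilot of a CE-marked Class I device with reactions expected to be uncommon, and about 26% power would usually miss a doubling. That limits the importance of the point and argues against a test. It does not favour a summary with no comparator over one that has it.

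**Conclusion.** The point holds in a limited form. The only safety outcome listed, and the only safety summary the text says the committee reviews, are defined by attribution that rests on an unblinded nurse's opinion, although serious events are recorded in both arms regardless of relatedness. Followed as written, the outcome cannot show an excess of serious events that are not attributed to the socks. This is a stated restriction worth correcting, not a loss of data and not evidence that safety information is withheld from anyone.

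Its size cannot be fixed from the documents. Under the assumed 10% and 20% rates, 4.5 and 9 expected events would appear as 0 against anything from 0 to 9, depending on how readily events are attributed. The conclusion needs only the definitions; those rates serve as illustration. It concerns serious events only and makes no claim about which non-serious events should be recorded.

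**What to change.** 1. **Other secondary outcome measures:** replace the present safety item with *all serious adverse events by arm regardless of relatedness, and adverse device effects in the sock arm*.
2. **Adverse and serious adverse events:** state that the committee receives cumulative counts of all recorded serious events by coded arm, with falls identifiable, alongside the existing summary of adverse reactions. The reaction summary should not carry the arm codes, since it would reveal which arm is which.
3. State that the table is descriptive and that no between-arm test is planned.

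The cost is wording in two sections and one extra table per committee report, built from data already collected. The small downside is that committee members see safety data by arm, which matters little in an open pilot.
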